## Objective 2:

Collect qualitative and quantitative data regarding the type and functionality of existing sanitation infrastructure at the household level through a participant-administered and observational survey.

### Demographic Survey

The team will conduct a demographic survey in person during the first household visit for sampling. The demographic survey will be self-administered by a participant at each of the 50 households unless the participant specifies otherwise. This survey is intended to gather information about the characteristics of the enrolled participant and the household as well as contact information for future sampling and surveys. Each survey will be administered through Qualtrics (https://unc.az1.qualtrics.com/) and will include multiple-choice and open-ended questions. Questions will include but not be limited to the participant’s gender and race/ethnicity, household income range, and preferred method of future contact.

### Sanitary Inspection Survey

The team will conduct observational and participant-taken sanitary inspection surveys in person or over the phone pre- and post-intervention. The observational survey will be conducted at all 50 households by the enumerator and is intended to elucidate current management practices for wastewater at the home as well as to document any visual damages to existing infrastructure. The written participant sanitation surveys will be self-administered by a participant at each of the 50 households unless the participant notes otherwise and are intended to gather information about each household’s water and sanitation practices. Each survey will be administered through Qualtrics (https://unc.az1.qualtrics.com/) and will include multiple-choice questions, open-ended questions, and photographs of current infrastructure. Questions will include where gray and black water is discharged, damage to infrastructure, and what type of water is used for drinking and hygiene.

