Without reliable and affordable alternatives, many households use what is known locally as “straight piping.” Straight-piping consists of a pipe that transports untreated wastewater (black water and/or gray water) directly from the home to an uncontained pit, ditch, stream, waste field, or another “disposal area” where it is accessible to people and animals (16). The Alabama Center for Rural Enterprise claims that most straight pipes are less than 10 meters long, suggesting that discharge points are typically within close proximity to homes (15). It is difficult to find data that encapsulates the full scope of this issue since homeowners can face legal repercussions for discharging wastewater via straight pipes. The use of “inadequate sewage disposal systems” is a criminal misdemeanor in Alabama that could result in fines – as much as $500 for each citation – eviction, and – in some cases – arrest (7). Considering the barriers to municipal sewerage and failures of onsite sewage disposal systems and the gaps these create, there is a need for innovation in this space to identify technologies and infrastructure models suitable for rural regions such as the Black Belt.

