### Well-Being Survey

We will collect data on participant well-being through a survey. The team will conduct surveys with a participant representing each of the 50 households enrolled in this study. The surveys will be conducted either in person or by phone at two time points, once before and once after the implementation of the community-wide sanitation system. These surveys will attempt to capture how limited access to sanitation services affects the overall well-being such as distress, fear of legal ramifications, and management related concerns. The surveys will be administered through Qualtrics (https://unc.az1.qualtrics.com/) through a combination of multiple-choice and open-ended questions. If the participant consents, the well-being survey will be recorded and transcribed. The outcome for Objective 4 is an assessment of changes in participants’ quality of life by comparing well-being before and after connection to the wastewater intervention.

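### The phone option as worded covers the enumerator's visual inspection, and survey mode may differ between a household's pre and post surveys, which could bias the secondary contrasts in Objectives 2 and 4

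*Protocol article*

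**What the plan says.** Three parts of the protocol article bear on this point.

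- **Sanitary Inspection Survey (Objective 2).** The opening sentence sets the mode for both instruments together: "The team will conduct observational and participant-taken sanitary inspection surveys in person or over the phone pre- and post-intervention". The next sentence describes the first instrument: "The observational survey will be conducted at all 50 households by the enumerator", with a purpose that includes to "document any visual damages to existing infrastructure". The participant's own survey is described as written and normally self-administered, and the surveys include photographs of the infrastructure.
- **Well-Being Survey (Objective 4).** "The surveys will be conducted either in person or by phone at two time points, once before and once after the implementation" of the new system. The content is "overall well-being such as distress, fear of legal ramifications, and management related concerns". Audio recording depends on the participant's consent.
- **Timing and use.** Methods and analysis places the sanitary surveys at time points 2 and 5 and the well-being surveys at 3 and 6. Research Objectives and Hypotheses expects failing systems and straight-pipe sites to become less common (Objective 2) and quality of life to improve (Objective 4). Both objectives are secondary.

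Background and Context explains why the subject is sensitive: using an inadequate disposal system "is a criminal misdemeanor in Alabama that could result in fines", and eviction or arrest are also mentioned.

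**The concern.** There are two linked problems.

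First, the mode rule conflicts with the instrument it governs. An enumerator on the phone cannot see damage or a discharge point. What is recorded is the participant's account, so the observational survey loses what distinguishes it from the participant-taken one. Intervention Fidelity and Adherence treats the observational and self-reported surveys as separate sources, so the distinction matters to the plan.

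Second, mode is open at each time, while the outcomes compare one time with the other. If the share of phone surveys differs between pre and post, any effect of mode on what is seen or disclosed is mixed with the effect of connection. The protocol gives its own reason to expect that answers might depend on mode, namely the legal exposure of households with straight pipes. The Bias section discusses reporting, courtesy and social desirability bias but not mode.

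At stake is the reading of two secondary objectives: the change in prevalence of failing systems and straight pipes, and the change in reported well-being.

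**Working it through.** **No plan figure to reproduce.** The article gives no sample size, power or expected difference for the survey outcomes. Its calculation (about 30 households) is for soil E. coli and does not enter here.

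**Step 1: the text.** The phrase allowing person or phone follows a joint subject, observational and participant-taken, so grammatically it applies to both. The sentence after it places the observational survey at the homes and gives it a visual purpose. The two cannot both hold for an observational survey done by phone. The Demographic Survey section, by contrast, fixes the visit as in person, so the article does specify mode where it chooses to.

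**Step 2: when a mode effect becomes bias.** Let *p* be the true prevalence of a visible discharge, the same before and after (no real change). Let detection be 1 in person and *s* by phone, and let *q0* and *q1* be the shares done by phone before and after. Then:

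- observed prevalence before = *p*[1 − *q0*(1 − *s*)]
- observed prevalence after = *p*[1 − *q1*(1 − *s*)]
- spurious change = −*p*(1 − *s*)(*q1* − *q0*)

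This is zero when *q1* = *q0*, negative (an apparent improvement) when phone use rises, and positive when it falls.

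**Step 3: illustrative size. All values are assumptions; none is in the documents.**

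| Assumed case | Arithmetic | Spurious change |
|---|---|---|
| *p* = 0.40, *s* = 0.70, all in person before, all by phone after | −0.40 × 0.30 × 1 | −12 points |
| as above, 10% non-disclosure | −0.40 × 0.10 × 1 | −4 points |
| as above, 50% non-disclosure | −0.40 × 0.50 × 1 | −20 points |
| *p* = 0.30, *s* = 0.90, a quarter by phone after | −0.30 × 0.10 × 0.25 | −0.75 points |
| *p* = 0.50, *s* = 0.60, all by phone after | −0.50 × 0.40 × 1 | −20 points |
| *p* = 0.40, *s* = 0.70, all by phone before, all in person after | −0.40 × 0.30 × (−1) | +12 points |
| any *p* and *s*, equal phone share | difference in shares is 0 | 0 |

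The 50 households less the 20 comparison households leave 30. Among those, 0.75 to 20 points is about 0.2 to 6 households.

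**Step 4: well-being.** The same logic applies to a mean score, with a mode shift in place of non-detection. The documents do not say whether phone would raise or lower reported distress or fear of legal consequences, so no sign can be assigned.

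**The case against.** **It is only loose drafting.** The enumerator works at the homes, looks for visible damage, and the surveys include photographs. The natural intention is inspection on site, with phone for the questionnaire. That is probably right, and it is why the point is modest. But the sentence as printed allows the other practice and should be corrected.

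**The fieldwork already guards against a hidden discharge.** At straight-pipe and cesspool homes the team samples soil at the point of impact and returns to the same locations at all six time points (Soil Sample Collection). At such homes not yet connected it also takes wastewater at the discharge site (Wastewater Sample Collection). Connection data are collected separately (Intervention Fidelity and Adherence). A household would have to conceal by phone something the team already knows about. This stands as a partial safeguard for Objective 2 and makes the larger figures above less likely. It does nothing for the well-being contrast, and neither Coding and Analysis nor the Well-Being Survey section states that these checks, or the comparison households, will be used to adjust the survey results.

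**Recording and matching mode are operational details a condensed article may omit.** Silence alone would not be a finding. The point rests on what is stated: a mode rule that contradicts one instrument and leaves mode open on both sides of a contrast.

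**Two stronger readings are tempting and not supported.** A reader might infer that a phone inspection defeats the safeguard against reporting bias in the Bias section. It does not: that safeguard is the environmental sample data, which survey mode does not touch. A reader might also infer that flexible mode will produce a false improvement. The documents do not show that the mode mix will differ, in which direction, or what effect phone has.

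**Conclusion.** The point holds in a limited form. The phone option as worded covers an inspection that requires sight of the site, and the plan lets mode differ between the two surveys of one household. A change in mode mix could therefore bias the pre-post contrasts of Objectives 2 and 4.

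Size and direction cannot be derived from the documents. The range of about 0.75 to 20 points rests on assumed prevalence (30% to 50%), non-detection by phone (10% to 50%), phone share after connection (25% to 100%), full detection in person and no phone use before. With an equal mode mix the spurious change is zero.

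The consequences are confined to secondary objectives. Objective 2's outcome is described under Coding and Analysis as a characterization, and Objective 4 is exploratory. The primary soil E. coli outcome and all environmental sampling are unaffected. This is a cheap improvement worth making, not a threat to the study's main conclusion.

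**What to change.** 1. In Sanitary Inspection Survey, state that the observational inspection is done on site at time points 2 and 5, during the sampling visits already planned, and that phone applies only to the participant questionnaire.
2. In Sanitary Inspection Survey and Well-Being Survey, state that a household's post survey uses the same mode as its pre survey where possible: in person or phone, and self- or interviewer-administered.
3. Record the mode at each survey, and run a sensitivity analysis that excludes households whose mode changed.
4. Do not require recording status to match. It depends on consent, and a participant may agree once and decline later.

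**Cost.** Wording changes and one extra data field. Drinking water is collected from all 50 households at each of the six time points, so on-site inspection should need no extra visits. The study began in August 2024, so some pre surveys may already be done; matching the post mode to the pre mode is still feasible if the pre mode is known. The downside is slightly less scheduling flexibility and possibly a few missed post surveys, which the words ‘where possible’ limit.

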### Coding and Analysis

We will code responses to the survey questions into appropriate categories and then import data into R for analysis (R Foundation for Statistical Computing, Vienna, Austria). The category codes that will be applied to the responses will be created deductively. Data collected in the surveys will be used to inform the characteristics of the participants of this study. The outcome for objective 2 is a characterization of the wastewater intervention’s potential impacts, such as how human waste is being treated and the observable quality of the household water supply.

## Objective 3:

Estimate the effects of the implementation of a community-wide sanitation system on the health risks associated with exposure to enteric pathogens and fecal indicators.

### Quantitative Microbial Risk Assessment Model

We will use a quantitative microbial risk assessment (QMRA) model to compare the annual risk of enteric infection between pre- and post-intervention settings. QMRA is a probabilistic modeling approach that combines pathogen-specific dose-response models and population-specific exposure assessments to characterize the risk of infection from microbial hazards (31–34).

We will estimate the risk of enteric infection under pre- and post-intervention settings using the data collected in Objective 1. From this dataset, we will use measures of prevalence of enteric pathogens and concentrations of pathogen gene targets to estimate a distribution of pathogens in soil under both pre- and post-intervention settings.

We will estimate the viability of the enteric pathogens using a ratio of culturable *E. coli* to gene copies of *E. coli* recovered from the environmental samples. Using the ingestion parameters for soil from the US EPA exposure factors handbook, we will estimate a daily exposure dose of viable enteric pathogens. Using published dose-response models, we will then estimate a daily and annual risk of infection for pathogens that are in more than 10% of the samples. We will use stochastic methods to propagate variability and uncertainty throughout the model (35). We will then use previously described methods to generate effect measures estimating attributable reductions in risk of infection between pre- and post-intervention settings (36). The outcome for objective 3 is a modeled estimate of the change in daily and annual risk of enteric infection due to environmental exposure through soil by comparing pre- and post-intervention soil conditions.

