We chose to use an ITS instead of a randomized controlled trial because in the context of community-wide infrastructure projects, randomized trials are infeasible and may come with additional equity and ethical concerns, regardless of the fact that health effects specifically attributable to sanitation are variable across trials (25,26). To address concerns that may arise in the absence of a randomized controlled trial, we will include a minimum of 10 additional households from a neighboring community that has existing adequate sanitation and 10 more comparison households with poor sanitation that will not be connected to the intervention until after the conclusion of this study. These 20 comparison sites will allow estimates of (1) background levels of fecal microbes in sample matrices and (2) the influence of non-intervention-related factors (e.g., flooding) on the presence and quantity of sanitation-related microbes. The comparison sites, along with the fact that we are sampling at multiple time points before and after the intervention, will allow us to account for temporal and spatial variation in microbial density.

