## Limitations:

### Secular trends in exposures or outcomes

Because ITS analyses compare pre- and post-intervention trends of outcome measures, a limitation of this approach is the existence of non-intervention, secular changes that obscure or complicate the attribution of effects to the point of intervention. Additionally, an ITS does not include a control group; therefore, simultaneous trends may be incorrectly attributed to the intervention itself. Weather-related events, such as rainfall and temperature, are examples of independent variables that could act as potential confounders because extreme rainfall or temperatures can increase blockages and breakages in onsite wastewater treatment systems (37). We will closely monitor rainfall and adjust our analyses to account for any differences observed by incorporating comparison sites. However, it is important to note that the potential for residual confounding cannot be eliminated completely in this study design. As previously described, we plan to include a minimum of 10 comparison sites with existing adequate sanitation and 10 comparison sites with poor sanitation that will not be connected to the intervention until after this study concludes. This plan will allow estimates of (1) background levels of fecal microbes in sample matrices and (2) the influence of non-intervention-related factors (e.g., flooding) on the presence and quantity of sanitation-related microbes.

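### Objective 3 calls a pre/post contrast in modelled infection risk attributable, without carrying in the comparison-site adjustment that the Limitations promise only in general terms

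*Protocol article*

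**What the plan says.** The section on the Quantitative Microbial Risk Assessment (QMRA) model in the protocol article sets out the calculation. "We will estimate the risk of enteric infection under pre- and post-intervention settings using the data collected in Objective 1". Prevalence and gene-target concentrations are used to "estimate a distribution of pathogens in soil under both pre- and post-intervention settings". After a viability ratio, a soil-ingestion dose and dose-response models, the plan is to derive effect measures for "attributable reductions in risk of infection between pre- and post-intervention settings", by methods cited to an earlier publication. The section closes by defining the outcome as a modelled change in daily and annual infection risk "due to environmental exposure through soil by comparing pre- and post-intervention soil conditions". It names no comparison household, projected trend or weather term.

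Three other places bear on this:

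- Limitations, Secular trends in exposures or outcomes, cautions that "simultaneous trends may be incorrectly attributed to the intervention itself" and gives rainfall and temperature as possible confounders. The same paragraph says that rainfall will be monitored and that the analyses will be adjusted by bringing in the comparison sites. It gives no method and does not name Objective 3.
- Interrupted Time Series provides for "10 more comparison households with poor sanitation that will not be connected to the intervention until after the conclusion of this study". One stated purpose of the comparison sites is to estimate "the influence of non-intervention-related factors (e.g., flooding) on the presence and quantity of sanitation-related microbes".
- Soil Sample Collection excuses only the adequately served homes from impacted-soil sampling. Methods and analysis sends all soil samples to the qPCR panel.

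**The concern.** The objective is worded causally: it sets out to estimate the effects of the sanitation system on health risk. The contrast that the section defines is before versus after. Such a contrast equals the intervention effect only if soil pathogen levels would otherwise have stayed the same, and the protocol's own Limitations say that this cannot be assumed.

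The primary regression at least models a pre-intervention trend. The Objective 3 text does not mention one, so the warning applies to it at least as strongly. Adjusting the primary regression would not carry over, because that regression concerns culturable *E. coli*, whereas the risk model takes pathogen prevalence and gene-target concentrations as inputs. The viability ratio also comes from the environmental samples, so it too could shift between periods if estimated separately in each.

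At stake is the study's quantitative estimate of infection risk. A wetter or drier post-connection period could be reported as harm or benefit from the sewer.

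**Working it through.** Objective 3 states no effect size or precision target, so there is no figure of the plan's to reproduce. The text settles the main point, and the arithmetic only gives a sense of scale.

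**1. Is the contrast fixed as pre versus post?** Yes. The pathogen distributions, the effect measures and the closing outcome definition all refer to those two settings and no others.

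**2. Are data for a concurrent comparison collected?** Yes. The 10 poor-sanitation comparison homes remain unconnected during the study. They are not among the homes excused from impacted-soil sampling, and their soil goes through the same qPCR panel. No new sampling or assay is needed.

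**3. Size if nothing is adjusted.** Assumptions: log10 units, no true effect, risk proportional to dose (the low-dose range), and a background fall of *s*. The documents give no value for *s*.

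Apparent reduction = 1 − 10^(−*s*)

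- *s* = 0.1: 1 − 0.794 = 21%
- *s* = 0.2: 1 − 0.631 = 37%

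**4. Direction.** Take a true fall of 0.45 log10, borrowing the effect size from Sample Size Calculations purely as an example: 1 − 10^(−0.45) = 64.5%.

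- With a background rise of 0.2: 1 − 10^(−0.25) = 44%
- With a background fall of 0.2: 1 − 10^(−0.65) = 78%

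The error can understate a benefit as easily as overstate it.

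**5. Annual risk.** The section also reports annual risk, which saturates. Assume 365 independent days with daily risk *p*, so that annual risk = 1 − (1 − *p*)^365. Apply a background fall of 0.2 log10, which multiplies *p* by 0.631:

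- *p* = 0.0001: annual risk goes from 0.0358 to 0.0228, a fall of about 36%
- *p* = 0.01: annual risk goes from 0.974 to 0.901, a fall of about 8%

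The 37% therefore applies to daily risk and to low annual risk, and shrinks as annual risk approaches 1.

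**6. Precision of an adjusted contrast.** Assume 30 connected homes (50 minus 20 comparison homes, inferred), 10 unconnected homes, three visits before and three after, and the pilot within-household variance of 4.3. That variance is for an *E. coli* gene target and stands in here for the pathogens.

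- Variance of one home's pre/post change, one sample per visit: 4.3 × (1/3 + 1/3) = 2.87
- SE, connected homes only: √(2.87/30) = 0.31 log
- SE, connected minus unconnected: √(2.87/30 + 2.87/10) = 0.62 log
- With three independent samples per visit: 0.18 and 0.36 log

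In both cases the SE doubles, since √[(1/30 + 1/10)/(1/30)] = 2.

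**The case against.** The best defence is the Limitations paragraph itself. It promises adjustment of the analyses, in the plural, using comparison sites. Those sites exist to capture outside influences on the presence and quantity of microbes, which are the inputs to the risk model. The model draws on Objective 1 data, which include the comparison homes, and the effect measures follow a cited method that is not available here and might contain a comparator. A condensed article may also leave such detail to a fuller document.

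Part of this stands. A reader might infer that no comparison household enters the risk calculation at all. The documents do not establish that: they say neither that comparison homes enter nor that they are left out. What the defence does not remove is that the article itself fixes the outcome as pre versus post and itself chooses the word attributable. That is a stated definition, not an omitted detail, and the general promise is not linked to it.

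A reader might also infer that most of any reported reduction will be background drift, for example by setting the drift at 0.45 log10. That value is the planned intervention effect, not an estimate of background change, and the documents supply no such estimate. Staggered connection also means that a single weather event need not fall on the same side of connection for every home. This lessens the bias without removing it.

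Finally, Objective 3 is secondary and is described as a modelled estimate, and an adjusted contrast resting on 10 homes is imprecise. Both points are fair. They bear on how strongly to press the change and on how to report the result.

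**Conclusion.** The point holds in limited form. The Objective 3 text pairs a causal label with a before/after contrast and does not bring in the comparison-site adjustment that the Limitations promise in general terms. Followed as written, it would credit background change in soil pathogens to the sewer, in either direction.

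The scale of 21% to 37% in daily risk for a 0.1 to 0.2 log10 background fall rests on assumed drift, no true effect and low-dose proportionality. It illustrates sensitivity and does not predict the bias in this study. For annual risk the figure can be much smaller. The change should be made because it uses data already planned, but the outcome is secondary and the primary analysis is not affected.

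**What to change.** In the QMRA section:

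1. Run the same model on the 10 unconnected poor-sanitation homes. They have no connection date, so assign their samples to pre or post by the calendar sampling rounds of the connected homes, and state that rule in advance.
2. Report the post/pre risk ratio for connected homes beside that for unconnected homes, together with the ratio of the two. Propagate the uncertainty of both groups through the simulation.
3. Use the word attributable only for the comparison-adjusted estimate. Call the unadjusted result a pre/post difference, and continue to report it under that name.
4. Say explicitly that this is how the adjustment promised in the Limitations applies to Objective 3.

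The cost is one further model run, the assignment rule and some rewording, with no extra sampling. The price is precision. The log-scale SE roughly doubles in the illustration with 30 and 10 homes, and the adjusted ratio may be uninformative for pathogens only just above the 10% inclusion threshold. For that reason the adjusted estimate should accompany the pre/post difference and not replace it.
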